**Figure 1 Study Schema**

### 3.1 Study Design Rationale

Although clinical manifestations of asthma are well characterized the underlying molecular and cellular events that play a role in its development and progression are not yet well understood. This lack of understanding hampers the development of more effective asthma therapies. This study is designed to better understand the cell types and molecular mediators that characterize specific asthma severity phenotypes (mild, moderate and severe asthma). Biomarker analysis of blood and induced sputum at the cellular, protein, and mRNA levels will enable better understanding of asthma phenotypes. In addition histological, cellular and mRNA analysis of endobronchial biopsy and epithelial brushing samples will allow for bringing a bedside understanding of the disease to bench-side understanding of research animal models. This information will facilitate the identification of new therapeutic targets for asthma, the discovery of novel therapeutics for those targets and patient stratification for existing therapeutics.

Asthma has a heterogeneous disease etiology and is clinically presented in a broad range of severity. The diagnosis of asthma is based on characteristic symptoms, physician confirmation of the diagnosis, and confirmation of bronchodilator FEV1 reversibility. If confirmation of bronchodilator FEV1 reversibility is lacking, then evaluation of airway hyperreactivity to methacholine may be used to confirm the diagnosis. If hyperreactivity to methacholine cannot be performed at screening due to a low FEV1, or the subject does not have historical data to document hyperreactivity, then, an obstructive airway deficit as demonstrated by a FEV1/FVC ratio of  $\leq 0.7$  may be used to support the diagnosis.

The inclusion and exclusion criteria detailed in Section 4 of this protocol should enroll true asthmatic subjects and reduce the chances of enrolling subjects with other pulmonary conditions into this study. The inclusion of asthmatic subjects in the mild, moderate, and severe categories will provide important information about the pathobiology that accompanies these clinical categories. The healthy subjects will be screened for the absence of atopy, asthma, or other pulmonary conditions. Serial measurements over 12 months in the asthmatic subjects will allow reproducibility and stability of the initial phenotypes to be assessed.

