#### **4.2.2 Exclusion Criteria**

Subjects who meet any of the following criteria will be excluded from participating in the study:

1. Be considered, in the opinion of the investigator, to be an unsuitable candidate for the study.
2. History of any clinically significant medical illness or medical disorders including (but not limited to) cardiovascular disease, neuromuscular, hematological disease including bleeding disorders, respiratory disease, hepatic or gastrointestinal (GI) disease, neurological or psychiatric disease, ophthalmological disorders, neoplastic disease, renal or urinary tract diseases, or dermatological disease.
3. Diagnosis of chronic obstructive pulmonary disease (COPD), cystic fibrosis, or other significant respiratory disorder including significant occupational or environmental exposures with ongoing respiratory symptoms.
4. Have a bronchodilator response of  $\geq 12\%$  and at least 200 mL from baseline or an FEV1 value  $< 85\%$  of predicted value at screening.
5. A known history of sleep apnea requiring medical intervention.
6. Major or traumatic surgery within the 3 months prior to screening.
7. Have a positive urine pregnancy screening result.
8. Have a recent history (within previous 6 months) of alcohol or drug abuse.

9. Positive urine toxicology screen for substances of abuse, including but not limited to amphetamines, barbiturates, benzodiazepines, cannabinoids, cocaine, methadone, opiates and tricyclic antidepressants.
10. Have a positive urine screen for nicotine (urine cotinine test).
11. Have a positive breath test for alcohol at initial screening visit.
12. Have a positive serology test for HIV antibodies, hepatitis B surface antigen (HBsAg), or hepatitis C virus antibody (anti-HCV) at screening.
13. Have a positive Phadiatop test.
14. Donated blood (volume  $\geq$  500 mL) within 56 days prior to screening.
15. Received an experimental antibody or biologic therapy within the 6 months prior to screening, or received any other experimental therapy or new investigational agent within 60 days or 5 half-lives (whichever is longer) of study start.
16. Be unable or unwilling to undergo multiple venipunctures because of poor tolerability or lack of easy access to veins.
17. Is an employee or employee family member of the investigator, study center, or Sponsor.
18. Any condition that, in the opinion of the investigator, would complicate or compromise the study, or the well-being of the subject.

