### **4.3 Subjects with Asthma**

#### **4.3.1 Inclusion Criteria for Asthmatic Subjects**

Subjects must satisfy all of the following criteria to be enrolled in the study:

1. Must have signed an informed consent indicating that they understand the purpose of and procedures required for the study and are willing to participate in the study.
2. Be willing and able to adhere to the study visit schedule and other protocol requirements.
3. Be between 18 and 70 years of age, inclusive, at informed consent. Subjects who elect to undergo bronchoscopy must be between 18 and 55 years old, inclusive, at informed consent.
4. Have no clinically significant abnormalities as determined by medical history, physical examination, blood chemistry assessments, hematologic assessments including CBC, urinalysis (see [Attachment 2](#) for clinical laboratory analyses), measurement of vital signs, and ECG.
5. Have a BMI  $\leq$  32 kg/m^2.
6. Must be able to produce an adequate induced sputum sample at screening, defined as a selected plug weight of at least 50 mg and a squamous cell count of  $<$  20% (see Study Reference Manual).

7. Be a non-smoker for  $\geq 1$  year prior to screening and have  $\leq 10$  pack- year history of smoking.
8. No contraindications to the procedures in this study.
9. Symptoms compatible with asthma for at least 6 months prior to screening (wheezing, dyspnea, chest tightness), PI confirmation of diagnosis of asthma of any severity and exclusion of alternative diagnoses, and at least 1 one the following, tested sequentially at screening or based on historical documentation:
  - Bronchodilator reversibility after inhalation of SABA at screening or documented within the previous 24 months defined as an increase in  $FEV_1 \geq 12\%$  and at least 200 mL from baseline. If reversibility is  $< 12\%$  and per the opinion of the PI, a repeat bronchodilator reversibility test is performed; this result may be used for subject enrollment.
  - PC20 methacholine  $\leq 16$  mg/mL at screening or documented within 24 months prior to screening. If the PC20 is  $> 16$  mg/mL, the subject is ineligible.
  - Obstructive physiology defined as a  $FEV_1/FVC$  ratio  $< 0.7$ .
10. Fall into 1 of the categories for asthma severity (mild, moderate, or severe) as described in the study population (see Section 4.1).
11. Prebronchodilator  $FEV_1 \geq 50\%$  predicted at screening.

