## **7.1 Screening Procedures**

Prior to screening, the investigator (or designee) will explain the study's rationale, procedures, and risks, and ask each potential subject if they wish to consent to participate. After written informed consent has been obtained, each subject will be assigned a unique subject number and will be evaluated for each of the inclusion/exclusion criteria outlined in Section 4.2 (healthy subjects) or Section 4.3 (asthmatic subjects). Subject screening can be conducted over a period of up to 21 days.

For healthy subjects, the induced sputum procedure should take place after the results of Phadiatop and other inclusion/exclusion criteria have been met and laboratory assessments have been received.

For asthma subjects the PC20 methacholine test, if required for eligibility, and induced sputum procedure will be performed after other inclusion/exclusion criteria and laboratory assessments have been received.

If a subject is not able to produce an acceptable sample of sputum, he/she may return for a second attempt during the screening period. The second sputum induction should occur no earlier than 48 hours post first attempt and during the 21 days of the screening period.

If the result of a screening assessment is abnormal, the assessment may be performed a second time at the discretion of the investigator and sponsor. In such cases, the first abnormal test result will not constitute a screen failure; however, a second clinically significant abnormal result will be considered a screen failure. A subject will not be enrolled in the study if results of tests performed at screening, or, if applicable, at the time of a second test indicate that the subject is ineligible to participate.

For subjects who are not eligible for this study due to screening virology serology test results, consultation with a physician with expertise in the treatment of such infections is recommended.

For asthmatic subjects who do not meet asthma inclusion/exclusion criteria (based on investigator and sponsor judgment and/or medication history) or do not meet the spirometric criteria, an additional assessment of asthma and/or spirometry can be done within 2 weeks of initial screening. In such cases, the first abnormal test result will not constitute a screen failure; however, a second clinically significant abnormal result will be considered a screen failure.

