### **7.2.2 Bronchoscopy Visit**

A bronchoscopy and attendant procedures will be performed during this visit and should occur within 5 to 14 days after the baseline visit. Details of the bronchoscopy procedure are described in the Study Reference Manual.

Healthy subjects should meet the following criteria, or the bronchoscopy visit should be postponed until the subject can meet these prerequisites.

- No intercurrent illness in the 14 days prior to the bronchoscopy including upper respiratory tract infections, etc.
- Post-bronchodilator  $FEV_1 \geq 80\%$  predicted that has not declined by more than 10% from screening. For example, if baseline  $FEV_1$  is 3.86 liters, a decrease of  $\geq 386$  mL would render the subject ineligible for the bronchoscopy on that day.
- Healthy subjects who cannot complete the bronchoscopy visit within 14 days of the baseline visit will be given an additional 14 days to complete the procedure. If the subject could not complete the bronchoscopy after the additional 14 days they will be discontinued from the study.

Asthmatic subjects should not withhold any inhaled medications before the bronchoscopy visit. A pre- and post-bronchodilator reversibility test will be performed prior to the bronchoscopy. The postbronchodilator  $FEV_1$  from this test serves as the prebronchoscopy  $FEV_1$  baseline determining eligibility. Asthmatic subjects must meet the following criteria or the bronchoscopy visit should be postponed until the subject can meet these prerequisites.

- Must be between 18 and 55 years of age, inclusive, at informed consent.
- Clinically stable asthma for at least 14 days prior to the bronchoscopy procedure, as defined by:
  - no clinically significant worsening of asthma requiring augmentation of therapy (eg, increased use of rescue medications, antibiotics, systemic steroids, increased controller medications, hospitalization) as per judgment of the investigator,
- Post-bronchodilator  $FEV_1 \geq 60\%$  predicted that has not declined by more than 10% from screening. For example, if baseline  $FEV_1$  is 2.56 liters, a decrease of  $\geq 256$  mL would render the subject ineligible for the bronchoscopy on that day.
- No intercurrent illness in the 14 days prior to the bronchoscopy including upper respiratory tract infections etc.

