### **Attachment 1.1 Study Assessments for Healthy Subjects**

- i. Supine vital signs should be measured after 10 minutes of rest and include temperature, resting pulse rate, and blood pressure. When scheduled concurrently with a blood draw or ECG, vital signs should be measured after the ECG and before the blood draw.
- j. Pregnancy test will be performed for all female subjects prior to study procedures.
- k. Only adverse events related to study procedures should be recorded.
- l. Healthy subjects will be excluded if the pre-bronchodilator FEV1 value is < 85% of predicted value, and bronchodilator response is ≥ 12% and at least 200 mL.
- m. The post bronchodilator FEV1 value obtained at this visit serves as eligibility criterion for induced sputum if the induced sputum procedure is performed within 60 minutes. This FEV1 value also serves as the pre-induction FEV1 baseline and as a reference for post procedure FEV1 recovery value.
- n. Post bronchodilator spirometry will be performed at this visit if subjects' post procedure FEV1 does not return to 80% of pre induction FEV1 baseline. (see Study Reference Manual).
- o. Pre- and postbronchodilator FEV1 values are assessed before bronchoscopy and the postbronchodilator FEV1 serves as the prebronchoscopy baseline for eligibility and safety monitoring. After the bronchoscopy, a short-acting bronchodilator may be administered and spirometry is repeated (see Study Reference Manual).
- p. If a subject does not produce a valid sputum sample at screening, they may be given a second opportunity to do so within the screening window (21 days). Sputum Induction may be repeated at the baseline visit, if required, within the 7 day window for this visit. The second sputum induction should occur no earlier than 48 hours from first attempt for both the screening and baseline visits.
- q. Subjects will be required to remain overnight in the study unit for follow-up if, based on the clinical judgment of the Investigator, a subject is unfit for discharge. Subjects will undergo reassessment, including spirometry, the following day and will be discharged based on the Investigator's assessment of the subject's well being. See Section 7.2.2 and the Study Reference Manual for follow-up procedures.
- r. Requires an additional informed consent from the subject.

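### Footnote l of the healthy-subject schedule joins the two lung-function exclusions with *and*, where exclusion 4 in Section 4.2.2 joins them with *or*; a site relying on the footnote could admit controls whom Section 4.2.2 excludes

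*Protocol*

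**What the plan says.** Section 4.2.2 states how its list works: "Subjects who meet any of the following criteria will be excluded from participating in the study". Exclusion 4 in that list gives two lung-function findings at screening, a bronchodilator response of at least 12% and 200 mL, and an FEV1 under 85% of predicted. The words joining them are "and at least 200 mL from baseline or an FEV", followed by the 85% limit. Either finding is enough to exclude.

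Attachment 1.1 attaches footnote l to both the pre- and the post-bronchodilator spirometry entries at screening. It says that healthy subjects are excluded if pre-bronchodilator FEV1 is below "85% of predicted value, and bronchodilator response is ≥ 12% and at least 200 mL". Read literally, both findings are needed.

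Three other statements bear on the point:

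- Section 3.1, on intent: "The healthy subjects will be screened for the absence of atopy, asthma, or other pulmonary conditions".
- Section 7.1, on which list applies: each subject is "evaluated for each of the inclusion/exclusion criteria outlined in Section 4.2 (healthy subjects").
- Section 7.2.2, on the day of bronchoscopy: a healthy subject needs a post-bronchodilator FEV1 of at least 80% "predicted that has not declined by more than 10% from screening". It sets no limit on reversibility.

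**The concern.** Two current statements of one eligibility rule give different answers, and the looser one sits where staff read the screening spirometry result.

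The healthy cohort is the only comparator. Section 9.2 uses it to find biomarkers that differ between asthma and health, and to decide whether a profile seen in some asthmatics also occurs in healthy people. Controls with reversible or reduced airflow would tend to shrink the first contrast and muddy the second.

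Spirometry is also the only objective airway test scheduled for controls. Attachment 1.1 has no methacholine challenge and no FENO, and Section 7.6 confines FENO to asthmatic subjects. The Phadiatop test addresses atopy, and inclusion 8 (no chronic respiratory disease) rests on history. If the spirometry rule is loosened, no other measurement does its work.

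**Working it through.** The plan gives no figure to reproduce here, so the check compares the two rules and then follows each affected subject through the later visits.

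**Inputs.** R = response of at least 12% and at least 200 mL; L = FEV1 below 85% predicted (Section 4.2.2, exclusion 4; Attachment 1.1, footnote l). Bronchoscopy-day threshold: post-bronchodilator FEV1 at least 80% predicted (Section 7.2.2). Planned controls: 30. Adequate bronchoscopy samples: 80% (Section 9.2). First interim look: 15 healthy subjects (Section 9.3).

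**Step 1: the two rules.**

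| Finding at screening | Exclusion 4 (R or L) | Footnote l (L and R) |
|---|---|---|
| Neither | not excluded | not excluded |
| R only | excluded | not excluded |
| L only | excluded | not excluded |
| Both | excluded | excluded |

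They disagree in 2 of 4 cells.

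**Step 2: worked cases, with an assumed predicted FEV1 of 4.0 L.**

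- R only: 3.6 L before and 4.1 L after. 3.6/4.0 = 90% predicted; rise 0.5/3.6 = 13.9%, or 500 mL. Exclusion 4 removes this person; footnote l does not.
- L only: 3.1 L before and 3.3 L after. 3.1/4.0 = 77.5% predicted; rise 0.2/3.1 = 6.5%. Exclusion 4 removes this person; footnote l does not. The post-bronchodilator value is 3.3/4.0 = 82.5%.

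**Step 3: what the later visits would catch.**

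- R only: reversibility is measured again at baseline and before bronchoscopy, but no exclusion is tied to it. This person's post-bronchodilator FEV1 is 4.1/4.0 = 102.5% predicted, well above 80%. No later lung-function rule applies.
- L only, assuming bronchoscopy-day values like those at screening:
  - From 80% to under 85% predicted, the 80% check is met even with no response.
  - Below 80%, a response under 12% can still reach 80% if the starting value is above 80/1.12 = 71.4%. The 77.5% case above passes this way.
  - At 71.4% or below, a response under 12% cannot reach 80%, so the check stops the subject.

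The check is therefore partial. It also comes after the baseline visit, where Attachment 1.1 schedules induced sputum, serum, urine and whole blood for RNA.

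**Step 4: weight of one such control.**

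- Of all planned controls: 1/30 = 3.3%.
- Of adequate bronchoscopy samples: 30 × 0.80 = 24, and 1/24 = 4.2%.
- At the first interim look: 1/15 = 6.7%.

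**The case against.** The strongest reply is that footnote l admits nobody. It names one group to be excluded and does not say that everyone else is eligible. Its excluded group lies wholly inside that of exclusion 4, so a site applying Section 4.2.2 also satisfies the footnote. Section 7.1 makes Section 4.2 the list to check, Section 7 describes the schedule as a summary of frequency and timing, and Attachment 1.1 has its own eligibility row at screening. The comma before *and* might even be a loose way of listing two separate exclusions. All of this stands as a reason to expect few errors. It does not remove the conflict: the literal wording is a conjunction, and it states an exclusion rule on the rows where the test is read.

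Three stronger readings are tempting, and the protocol does not support them.

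- **A reader might infer a count.** If 5% to 10% of otherwise eligible volunteers had exactly one finding, 30 × 0.05 = 1.5 to 30 × 0.10 = 3 controls would be wrongly admitted. That prevalence has no source in the protocol, and the sum supposes that every site uses the footnote in place of Section 4.2.2.
- **A reader might infer that any low-FEV1 control reaches the bronchoscopy set.** A person at 75% predicted needs a rise of 80/75 − 1 = 6.7% to pass the bronchoscopy-day check. With no reversibility that person would be postponed and, after the extra 14 days, discontinued.
- **A reader might infer that a reversible control meets the asthma definition.** Reversibility is one element of inclusion 9 in Section 4.3.1, which also needs at least 6 months of symptoms and the investigator's confirmation of the diagnosis. Controls must also have no history of chronic respiratory disease or allergic symptoms and must not have a positive Phadiatop test.

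The study is also exploratory, with no formal hypothesis test, so no error rate is at stake. One or two such controls could not by themselves form a subset under the minimum of 5 in Section 9.2, although they could add to one.

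**Conclusion.** The contradiction is real and lies between two passages of current text. The rules differ for subjects with reversibility alone and for those with low FEV1 alone. Harm arises only where a site relied on the footnote. In that case the reversibility-only control passes every later lung-function rule, and the low-FEV1-only control is stopped in part and after baseline samples are taken.

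The number affected is probably small, given Section 7.1, and cannot be derived from the protocol. The percentages per control assume the planned 30 and the stated 80% sample yield. The protocol does not establish that controls were wrongly enrolled or that the contrasts are biased. The point still merits correction, because it concerns an operative entry rule for the only comparator group and costs almost nothing to settle.

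**What to change.** 1. Reconcile the two passages. Section 7.1 makes Section 4.2 the governing list, so footnote l should state the same rule as exclusion 4 or, more safely, just refer to it. While doing so, settle whether exclusion 4 means pre-bronchodilator FEV1: the footnote says so and Section 4.2.2 does not.
2. List the screening spirometry (FEV1 as percent predicted, and response in percent and mL) of all controls already enrolled, and flag any who meet exclusion 4.
3. If any are flagged, report the healthy contrasts with and without them.

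The cost is a one-word or one-line change to a footnote, a listing from data already collected, and a repeat of the healthy contrasts if the listing is not empty.

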**Attachment 1.3 Study Assessments for Asthmatic Subjects Not Receiving a Bronchoscopy**

- o. PC20 methacholine is done at screening if FEV1 bronchodilator response is < 12% and no documented reversibility or PC20 is available (see Sections 4.3.1 and 7.5).
- p. Some asthma medications are withheld prior to PC20 methacholine test. For detailed list of medications, see Study Reference Manual.
- q. PC20 methacholine test is performed at the baseline visit if not conducted at the screening visit.
- r. If a subject does not produce a valid sputum sample at screening, they may be given a second opportunity to do so within the screening window (21 days). Sputum induction may also be repeated at the baseline and 6-month biomarker Visit if required within the 7 day window for this visit. The second sputum induction should occur no earlier than 48 hours from first attempt for the screening baseline and biomarker visits.
- s. Sputum induction may be performed on the same day as PC20 methacholine test with the PC20 methacholine test being conducted first followed by induced sputum. The postbronchodilator FEV1 obtained after the PC20 methacholine test can serve as a pre sputum induction baseline value if sputum induction occurs within 60 minutes. This pre induction baseline FEV1 value serves to determine eligibility for sputum induction, which strength of saline should be used, and for safety monitoring (see Study Reference Manual).
- t. Requires an additional informed consent from the subject.
- u. Telephone contact should be made the day after the sputum induction procedure to collect any procedure related adverse events.
- v. The study coordinator should contact the subject by telephone 7 days and 24 hours before the baseline, bronchoscopy and 6 month biomarker visits to ensure that subject's asthma is well controlled before the visit.

